**Methods and analysis:**

Our study will be conducted across three distinct centers in Shanghai, Nanjing, and Suqian. The development of the smartphone-based multimodal AI system will take place in Shanghai with the goal of achieving ≥90% sensitivity and ≥95% specificity for diagnosing and triaging ophthalmic diseases. The first stage of the cross-sectional study will explore the system's performance in Shanghai's outpatient clinics. Medical histories will be collected without patient interaction, and anterior segment images will be captured using slit lamp equipment. This stage aims for ≥85% sensitivity and ≥95% specificity with a sample size of 100 patients. The second stage will take place at three locations, with Shanghai serving as the internal validation dataset, and Nanjing and Suqian as the external validation dataset. Medical history will be collected through patient interviews, and anterior segment images will be captured via smartphone devices. An expert panel will establish reference standards and assess AI accuracy for diagnosis and triage throughout all stages. A one-vs.-rest strategy will be used for data analysis, and a *post-hoc* power calculation will be performed to evaluate the impact of disease types on AI performance.

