### Statistical analysis

To assess the AI system's diagnostic and triage performance, we will use the one-vs.-rest strategy and calculate the area under the receiver-operating-characteristic curve (AUC), sensitivity, specificity, accuracy, positive predictive values and negative predictive values for disease diagnosis and subspecialty triage using IBM SPSS Statistics 26 software. Specifically, sensitivity measures the AI system's ability to correctly identify positive cases, such as diagnosing a specific disease or assigning a patient to the correct subspecialty. It is calculated by determining the ratio of true positives (correctly identified positive cases) to the sum of true positives and false negatives (missed positive cases). Conversely, specificity evaluates the AI system's capacity to accurately identify negative cases. For instance, it assesses the system's ability to correctly exclude the presence of a particular disease or to avoid assigning a patient to an incorrect subspecialty. Specificity is determined by calculating the ratio of true negatives (correctly identified negative cases) to the sum of true negatives and false positives (incorrectly identified negative cases). Accuracy, which indicates the proportion of correct classifications made by the AI system, will be determined as follows: Accuracy = (True positive + True negative)/(True positive + True negative + False positive + False negative). This parameter offers an overarching evaluation of the system's ability to make precise diagnoses and triage assignments. In addition to sensitivity, specificity, and accuracy, we will also calculate AUC, positive predictive values and negative predictive values. These parameters collectively provide a comprehensive assessment of the AI system's diagnostic and triage capabilities, ensuring a thorough evaluation of its performance. Subgroup analyses will be performed to explore the influence of lesion location (anterior segment disorders vs. posterior segment disorders) on the performance of the multimodal AI system. A *post-hoc* power calculation will also be conducted to assess how lesion locations influence the AI system's performance.

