### Sample size calculation

In the *in silico* development stage, the sample size is adjusted based on AI system performance. Initially, each subspecialty involves 20 medical dialogues, with 80% for training ChatGPT and 20% for validation. If ChatGPT cannot generate inquiries, diagnoses, and triage results in the validation dataset, we'll increase the dialogues. Next, 50 virtual cases for the top 1–5 diseases in each subspecialty are input into the diagnostic system. If the sensitivity and specificity of specific diseases do not meet the predefined thresholds (sensitivity ≥ 90%, specificity ≥ 95%), we will proceed to develop a disease-specific image-based diagnostic system. For each disease, we will compile a dataset consisting of 50 cases, including both anterior segment images and their corresponding diagnoses. This dataset will be randomly partitioned into training and testing sets, with the training set supporting system development and the testing set assessing diagnostic accuracy. Should the predetermined criteria (sensitivity ≥ 90%, specificity ≥ 95%) be satisfied, there will be no necessity for further expansion of the sample size.

For the silent evaluation stage, the primary objective is to achieve a sensitivity ≥ 85% and specificity ≥ 95% for diagnosing ophthalmic diseases. To meet this goal, we set sensitivity = 0.85, specificity = 0.95, statistical power (1-β) = 85, significance level (α) = 0.05, and the sample size for each disease is determined to be 22, following the methodology (Tests for One-Sample Sensitivity and Specificity) outlined in Pass15. Since this stage covers at least four different illnesses, we will include a minimum of 88 patients in the entire sample. To account for potential confounding factors, we have opted to include 100 patients in this phase.

For the early clinical evaluation stage, all subjects collected within predefined date ranges at three sites will be included. Data collection at the Shanghai and Nanjing sites spans from July 21 to August 20, 2023. At the Suqian site, data collection is scheduled from August 21 to August 31, 2023.

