## Discussion

Our study aims to develop a multimodal AI system based on ChatGPT-3.5 and explore its performance for the diagnosis and triage of ophthalmic diseases. Existing alternative proprietary LLMs include ChatGPT-4.0 and Google Bard (Lim et al., 2023). Additionally, there are some open source LLMs that can be locally deployed. As we plan to apply our designed multimodal AI system in clinical experiments, it necessitates swift interactive responses and the ability to handle parallel tasks. There are two primary reasons for not utilizing locally deployed LLM models. Firstly, their text generation performance is not as robust as ChatGPT, which hinders rapid interaction and concurrent conversations. Secondly, it demands a substantial amount of data for initial local training, which doesn't align with our objective of rapid product development and application in clinical experiments. ChatGPT currently stands out as the most proficient and reliable LLM product on the market for interactive applications. While ChatGPT-4.0 lacks support for prompt engineering, and Google Bard was not yet available at the outset of our research, we made the decision to develop our multimodal AI system based on ChatGPT-3.5.

One of the strengths of our multimodal AI system is its applicability to different ophthalmic diseases. Previous studies predominantly rely on photographs to detect certain ocular and visual abnormalities (Ting et al., 2019; Tan et al., 2021; Tiwari et al., 2022; Lou et al., 2023; Shao et al., 2023a). These image-centric technologies, while valuable, have limitations when it comes to large-scale applications across diverse ophthalmic conditions. The limitations primarily stem from the absence of comprehensive medical histories, which are crucial for accurate diagnosis (Ting et al., 2019; Moor et al., 2023). Therefore, we aim to integrate medical history inquiry with image-based diagnosis to empower a multimodal AI system. According to the protocol, we will evaluate the performance of this system in detecting most of the common ophthalmic diseases, including anterior and posterior segment disorders, strabismus, neoplasms, aesthetic abnormalities and ocular manifestations of systemic diseases. This system is efficient for triage procedures. During registration, pre-registration desk staff can assist patients with AI-powered diagnosis and triage, guiding them to subspecialty appointments.

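### The post-hoc power calculation is given a job it cannot do: power does not measure how lesion location (or, in the Abstract, disease type) influences performance

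*Protocol article*

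**What the plan says.** The Statistical analysis section of the protocol article first lists the performance measures: AUC, sensitivity, specificity, accuracy and the two predictive values. It then states: "Subgroup analyses will be performed to explore the influence of lesion location (anterior segment disorders vs. posterior segment disorders"). The next sentence adds a post-hoc "power calculation will also be conducted to assess how lesion locations influence the AI system's performance".

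The Methods and analysis paragraph of the Abstract describes what appears to be the same step, but there a post-hoc "power calculation will be performed to evaluate the impact of disease types on AI performance".

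Neither place fixes a difference between groups at which power would be evaluated. The Sample size calculation section plans no numbers for an anterior versus posterior comparison. For the early clinical evaluation it gives no number at all and takes whoever is enrolled within fixed calendar windows.

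**The concern.** The plan names a method and gives it a purpose that the method cannot serve. This is a stated choice of analysis, so it differs from detail that an article leaves to a fuller document. To learn how lesion location influences performance, one needs an estimate of the difference between groups and its uncertainty. Power supplies neither.

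The question matters for applicability. The system's image input is limited to the anterior segment, yet the Discussion expects it to be evaluated on common diseases "including anterior and posterior segment disorders, strabismus, neoplasms, aesthetic abnormalities and ocular manifestations of systemic diseases". Whether performance holds for posterior disease is something readers will want to know. A power figure presented as the answer could be misread: a low one taken to excuse a null comparison, a high one taken to support a positive comparison.

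The factor also differs between Abstract and Methods. Disease type can have many levels, while lesion location as defined has two, so it is unclear from the text which contrast the calculation concerns.

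**Working it through.** **The plan's own figure.** The article states no figure for post-hoc power or for the lesion-location comparison. Its only powered figure is for the silent evaluation ("the sample size for each disease is determined to be 22", and 4 × 22 = 88, raised to 100). That is a one-sample calculation per disease and says nothing about a difference between anterior and posterior disorders. Nothing below depends on it.

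**Reading 1: power at the observed difference.** For a two-sided z-test at α = 0.05 (the protocol's α; the two-sided form is my assumption), let z be the observed statistic, recovered from the two-sided p-value. Then

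observed power = 1 − Φ(1.96 − z) + Φ(−1.96 − z).

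| p-value | z | observed power |
|---|---|---|
| 0.01 | 2.576 | 73% |
| 0.05 | 1.960 | 50% |
| 0.20 | 1.282 | 25% |
| 0.50 | 0.674 | 10% |

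Sample sizes and proportions enter only through z. Once p is known, the power figure adds nothing.

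**Does it show the size of the influence?** The counts below are assumed for illustration; none come from the protocol. SE = √[p₁(1−p₁)/n₁ + p₂(1−p₂)/n₂], z = (p₁−p₂)/SE, and the CI is the difference ± 1.96 × SE.

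- 45/50 vs 40/50: difference 0.10, SE = √(0.09/50 + 0.16/50) = 0.0707, z = 1.414, p = 0.157, 95% CI −0.04 to 0.24, observed power 29%.
- 450/500 vs 430/500: difference 0.04, SE = 0.0205, z = 1.950, p = 0.051, 95% CI 0.00 to 0.08 (lower limit just below zero), observed power 50%.
- 54/60 vs 30/40: difference 0.15, SE = 0.0787, z = 1.907, p = 0.057, 95% CI 0.00 to 0.30 (lower limit −0.004), observed power 48%.

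The last two have nearly the same observed power although their differences are 0.04 and 0.15. Exchanging the two groups leaves p and power unchanged, so direction is lost too. The difference with its CI shows size, direction and precision.

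With the pooled two-proportion formula the link to p is nearly, not exactly, one-to-one. The same three examples give p = 0.161, 0.052 and 0.045, with power 28.6%, 49.5% and 51.7%.

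**Reading 2: power at a chosen difference, given the numbers enrolled.** Suppose 100 cases split 50/50 (assumed). The pooled formula gives 24% power for 0.85 vs 0.75 and 64% for 0.85 vs 0.65. These figures do not restate p. They depend only on the assumed proportions and the group sizes, so the system's actual performance in the two groups never enters. They cannot show how location influences it either.

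**What an interval would deliver at this size.** With a proportion of 0.85 in both groups and 100 cases, the CI half-width is 1.96 × √[0.85 × 0.15 × (1/n₁ + 1/n₂)]: 0.14 for a 50/50 split, 0.15 for 70/30 and 0.175 for 80/20 (assumed splits). If the aim of the power calculation was to convey how informative the comparison is, the interval already does this.

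**The case against.** The strongest reply is that the power calculation is an addition. The sentence before it plans the anterior versus posterior comparison, and the section lists the measures in which groups would be compared. This stands. A reader might infer that the lesion-location question would be left without any estimate; the text does not support that, because the planned subgroup analyses can supply one.

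Second, the article does not say that power will be computed at the observed difference. Post-hoc power can also mean power at the achieved sample size for a chosen difference, a plausible wish when the early clinical stage fixes no number. This stands as a limit: a reader might conclude flatly that the calculation only restates the p-value, but that holds under the first reading only. It does not rescue the sentence, because the second reading does not measure influence either.

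Third, the two-way split does not obviously accommodate conditions such as strabismus. A reader might infer that the plan needs a third group. A subgroup contrast need not include every case, the article does not say that all patients will be divided in two, and the classification of cases is detail that an article may leave to a fuller document. The same goes for the interval method and covariates.

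Fourth, anterior versus posterior is one way of grouping disease types, so the Abstract may simply be looser wording. That is fair; the mismatch is real but minor.

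Finally, no decision rule is tied to the power figure, so the misreadings described above are a risk and not something the article announces.

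**Conclusion.** The point holds in a limited form. The article assigns to post-hoc power the task of assessing how lesion location, or disease type, influences performance, and power cannot do that on either reading. At the observed difference, which is the natural reading because no effect size is fixed in advance, it is essentially a function of the p-value (about 50% at p = 0.05 and 25% at p = 0.20) and is silent on size and direction. The exact relation assumes a two-sided 5% z-test with the same standard error used for the test and for the power; with pooled variances it is approximate.

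The consequence is small. The analysis is exploratory, and no primary or secondary threshold or sample size in the article rests on it. It does not follow that the comparison itself is missing or that the primary results are at risk. It is still worth correcting, since an uninformative quantity is labelled as the answer to a question that readers will care about.

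**What to change.** 1. Delete the post-hoc power calculation from the Statistical analysis section and from the Abstract.
2. In the Statistical analysis section, state that the subgroup result is the anterior-minus-posterior difference in the planned performance measures, for example the proportion correctly diagnosed, with a 95% CI, reported as exploratory. The choice of interval method can be left to the analysis plan.
3. Name the same factor, lesion location or disease type, in the Abstract and the Methods.

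The cost is one sentence replaced in the Methods and one clause in the Abstract. No additional patients, data or measurements are needed, and the primary analysis is unchanged.

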### Sample size calculation

In the *in silico* development stage, the sample size is adjusted based on AI system performance. Initially, each subspecialty involves 20 medical dialogues, with 80% for training ChatGPT and 20% for validation. If ChatGPT cannot generate inquiries, diagnoses, and triage results in the validation dataset, we'll increase the dialogues. Next, 50 virtual cases for the top 1–5 diseases in each subspecialty are input into the diagnostic system. If the sensitivity and specificity of specific diseases do not meet the predefined thresholds (sensitivity ≥ 90%, specificity ≥ 95%), we will proceed to develop a disease-specific image-based diagnostic system. For each disease, we will compile a dataset consisting of 50 cases, including both anterior segment images and their corresponding diagnoses. This dataset will be randomly partitioned into training and testing sets, with the training set supporting system development and the testing set assessing diagnostic accuracy. Should the predetermined criteria (sensitivity ≥ 90%, specificity ≥ 95%) be satisfied, there will be no necessity for further expansion of the sample size.

For the silent evaluation stage, the primary objective is to achieve a sensitivity ≥ 85% and specificity ≥ 95% for diagnosing ophthalmic diseases. To meet this goal, we set sensitivity = 0.85, specificity = 0.95, statistical power (1-β) = 85, significance level (α) = 0.05, and the sample size for each disease is determined to be 22, following the methodology (Tests for One-Sample Sensitivity and Specificity) outlined in Pass15. Since this stage covers at least four different illnesses, we will include a minimum of 88 patients in the entire sample. To account for potential confounding factors, we have opted to include 100 patients in this phase.

For the early clinical evaluation stage, all subjects collected within predefined date ranges at three sites will be included. Data collection at the Shanghai and Nanjing sites spans from July 21 to August 20, 2023. At the Suqian site, data collection is scheduled from August 21 to August 31, 2023.

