### Hypotheses

For *in silico* development, our primary goal is to achieve a sensitivity of ≥90% and a specificity of ≥95% for diagnosing ophthalmic diseases. As a secondary outcome, we expect a positive predictive value of ≥90% and a negative predictive value of ≥95% for subspecialty triage of ophthalmic diseases.

For silent evaluation, the primary outcome is to achieve a sensitivity ≥ 85% and specificity ≥ 95% for diagnosing ophthalmic diseases. The secondary outcome is to achieve a positive predictive value ≥ 85% and a negative predictive value ≥ 95% for subspecialty triage of ophthalmic diseases.

For early clinical evaluation, we anticipate the primary outcome to reach a sensitivity ≥ 75% and specificity ≥ 95% for diagnosing ophthalmic diseases. For the secondary outcome, we expect a positive predictive value of ≥80% and a negative predictive value of ≥95% for subspecialty triage of ophthalmic diseases.

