### Recruitment

For the *in silico* development stage, all cases will be recruited at the Eye & ENT Hospital of Fudan University. Specifically, researchers will record doctor-patient conversations at each subspecialty clinic. The conversations will undergo a curation process that involves the removal of filler words and irrelevant content, resulting in the creation of medical dialogues. Eligible medical dialogues will be continuously enrolled from June 1 to July 1, 2023. Regarding the anterior segment images, researchers will browse medical records and consistently gather images related to the top 1–5 diseases in each subspecialty from January 1, 2020 to July 1, 2023. The initial sample size consists of 20 dialogues per specialty and 50 images per disease, which is then adjusted according to the AI system's performance.

For the silent evaluation stage, data will be continuously gathered in Shanghai from July 10 to July 15, 2023, with a sample size of 100 cases. Two pre-trained researchers will serve as observers in outpatient clinics, ensuring they do not interfere with standard management procedures. Upon obtaining the patients' consent (as detailed in Supplementary material 2), the researchers will collect the patients' medical information and enter it into the system. For patients who are prescribed with anterior segment imaging test by outpatient clinic doctors, the researchers will collect the images from the electronic medical system.

For the early clinical evaluation stage, eligible participants will be continuously recruited at three distinct sites. The Shanghai site serves as an internal validation dataset, with data collection spanning from July 21 to August 20, 2023. The Nanjing and Suqian sites function as external validation dataset, with data collection scheduled from August 21 to August 31, 2023. Each center will be staffed with two pre-trained researchers. These researchers will be responsible for patient recruitment across various subspecialty clinics within their respective centers. Once patients provide their consent (as detailed in Supplementary material 4) to participate in the study, the researchers will gather medical history and acquire anterior segment images. Following this, outpatient physicians will proceed with clinical diagnosis and treatment.

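### The rule that ends image collection for a disease is read on a fraction of 50 cases, so modules with true sensitivity of 80–85% meet the 90% target too often

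*Protocol article*

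**What the plan says.** All of this concerns the in silico development stage of the Protocol article.

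- **Target (Hypotheses).** For this stage, "our primary goal is to achieve a sensitivity of ≥90% and a specificity of ≥95" per cent.
- **Size (Sample size calculation).** If the dialogue-based system misses the thresholds for a disease, an image-based system is built: "For each disease, we will compile a dataset consisting of 50 cases".
- **Use of the cases (Sample size calculation).** "This dataset will be randomly partitioned into training and testing sets", "with the training set supporting system development and the testing set assessing diagnostic accuracy".
- **Consequence of a pass (Sample size calculation).** When both thresholds are met, "there will be no necessity for further expansion of the sample size".
- **Consequence of a fail (Recruitment).** The starting size is "50 images per disease, which is then adjusted according to the AI system's performance".

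Statistical analysis specifies a one-vs.-rest approach, so the denominator of a disease's sensitivity is that disease's own test cases. The article gives no derivation of the 50 and attaches no confidence bound to the thresholds at this stage. The only split ratio it states, "with 80% for training ChatGPT and 20% for validation", belongs to the dialogues.

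**The concern.** The gate compares a point estimate with 90%, and the denominator is only the held-out part of 50 cases. With so few positives, one or two images more or less on the right side change the decision.

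The two errors do not cost the same. A fail brings more data and another look. A pass stops collection for that disease, and the figure that triggered the stop becomes the stage's reported result. An 80% module that passes is reported at 90% or more, so its sensitivity is overstated by at least 10 percentage points. The rule therefore leans towards early, optimistic passes.

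What is at stake is the reliability of the stopping rule and of the development stage's primary result for each disease.

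**Working it through.** **Inputs.** 50 cases per disease, a random partition, accuracy read on the test part, and thresholds of 90% and 95% (Sample size calculation; Hypotheses). The test share for images is not stated. I assume 20% to 50%, that is 50 × 0.20 = 10 to 50 × 0.50 = 25 test positives. The lower end is what the dialogue ratio would give if it were applied to images.

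**No figure to reproduce.** The 50 is given without significance level, power, null value or precision target, so only the behaviour of the rule can be checked.

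**Formula.** With n test positives, the smallest passing count is r, which is 0.9n rounded up. At true sensitivity p, the chance of meeting the sensitivity condition is P(X ≥ r), with X binomial(n, p).

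Worked case, n = 10, r = 9:

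- p = 0.80: 10 × 0.8⁹ × 0.2 + 0.8¹⁰ = 0.268 + 0.107 = 0.376
- p = 0.85: 10 × 0.85⁹ × 0.15 + 0.85¹⁰ = 0.347 + 0.197 = 0.544

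| True sensitivity | 9/10 | 14/15 | 18/20 | 23/25 | 45/50 |
|---|---|---|---|---|---|
| 75% | 24.4% | 8.0% | 9.1% | 3.2% | 0.7% |
| 80% | 37.6% | 16.7% | 20.6% | 9.8% | 4.8% |
| 85% | 54.4% | 31.9% | 40.5% | 25.4% | 21.9% |
| 90% | 73.6% | 54.9% | 67.7% | 53.7% | 61.6% |
| 95% | 91.4% | 82.9% | 92.5% | 87.3% | 96.2% |

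The columns do not fall smoothly because r is rounded up: 14/15 is 93.3% and 23/25 is 92%.

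**Upper bounds.** A module must also show specificity of at least 95%. The chance of passing both conditions cannot exceed the chance of passing one, so each entry bounds the pass rate of the full rule from above. How far below it lies depends on the number of negatives, which is not stated.

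**Precision at a bare pass (exact 95% intervals).** 9/10: 55.5% to 99.7%. 23/25: 74.0% to 99.0%. 45/50: 78.2% to 96.7%.

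**Second look after a fail.** If a failed module were retested on a fresh, independent test set of the same size, the chance of passing within two looks is 1 − (1 − P)². For an 80% module this is 1 − 0.624² = 61% at n = 10 and 1 − 0.902² = 19% at n = 25. For an 85% module it is 79% and 44%. The retest size is an assumption, because the article does not say how an enlarged dataset is split.

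**All 50 tested.** The last column applies the same point-estimate rule to 50 out-of-fold predictions, treated as independent. Compared with 9/10 and 23/25, passes fall to 4.8% at 80% and 21.9% at 85%, while a 95% module passes more often (96.2% against 91.4% and 87.3%).

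**The case against.** Several objections have weight, and most of them limit the point rather than remove it.

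- **The test-set size is assumed.** An article may leave the split ratio to a fuller document, and its absence is not the complaint. The weakness is present across the range of 10 to 25, though much milder at 25.
- **The gate does not reject modules.** A reader might infer that it decides which modules enter the system, so that good modules are lost by chance. The documents do not support that. Meeting the thresholds ends enlargement, missing them brings more data, and no rule drops a module. A chance fail costs extra images.
- **The gate is not uninformative.** A reader might infer that it cannot tell a 75% module from a 90% one. At 23/25 the pass rates are 3% and 54%, and even at 9/10 they are 24% and 74%. The trouble lies nearer the threshold, at about 80–85%.
- **Patient overlap is not shown.** Recruitment counts images ("The initial sample size consists of 20 dialogues per specialty and 50 images per disease"), whereas Sample size calculation partitions cases. A reader might infer that one patient's images fall on both sides of the split. The article does not say that several images of a patient count as separate units, so this is only a possible risk that the mixed wording leaves open.
- **The remedy has limits.** A hold-out set is a standard design. At a true sensitivity of exactly 90%, testing all 50 fails 38% of the time, more than the 26% at 9/10 and less than the 46% at 23/25. The gain is in fewer false passes and in fewer fails at 95%.
- **Later stages re-test the system.** The silent and early clinical evaluations use new patients and their own thresholds. This stands, and it confines the harm to the development stage.

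**Conclusion.** The point holds in a limited form. Reading a 90% point-estimate gate on the test part of 50 cases lets an 80% module meet the sensitivity condition up to 38% (9/10) to 10% (23/25) of the time, and an 85% module up to 54% to 25%. A false pass stops data collection for that disease and makes the development stage's primary result optimistic.

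This rests on a test share of 20–50%, on independent test cases, on a single partition (the natural reading, though not spelled out) and on the sensitivity condition alone. It does not show that modules are wrongly excluded or that the clinical-stage results are wrong. It is worth correcting because the existing 50 cases can be used better at little cost.

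**What to change.** In Sample size calculation, replace the single random partition with 5-fold cross-validation at patient level, keeping all images of a patient in one fold. Each case is then predicted once by a model that has not seen it. Read the gate on all 50 out-of-fold predictions, report a 95% confidence interval beside the estimate, and then fit the deployed module on all 50. If the dataset is enlarged after a fail, repeat the procedure on the enlarged set. State the unit as patients in both Recruitment and Sample size calculation.

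**Cost.** Five training runs per module to read the gate, and no new images. The out-of-fold predictions are slightly dependent, so the interval and the pass rates above are approximate. Each fold's model is trained on 40 cases (50 × 4/5), so the estimate describes the training procedure rather than the final fit on 50. Modules with true sensitivity of 85–90% are still not sharply separated from the target, which is why the interval should be shown with the gate.

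### In silico image data are enlarged until 90%/95% is seen on the testing set, so the figures at the passing look are biased upward

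*Protocol article*

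**What the plan says.** The Hypotheses section gives the in silico stage its own target: "our primary goal is to achieve a sensitivity of ≥90% and a specificity of ≥95% for diagnosing ophthalmic diseases". It adds a secondary outcome on triage.

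Under Sample size calculation, for this stage "the sample size is adjusted based on AI system performance". Diseases that miss 90%/95% on virtual cases go to a disease-specific image system. For each of these, "we will compile a dataset consisting of 50 cases". Then: "This dataset will be randomly partitioned into training and testing sets". The testing set supplies the accuracy figure. If the 90%/95% criteria are met, "there will be no necessity for further expansion of the sample size".

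Recruitment confirms that the 50 images are only a starting size, "which is then adjusted according to the AI system's performance", and draws them from records of January 2020 to July 2023.

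For this stage the article gives no maximum size, no number of rounds, no split ratio for the images and no test set kept apart from the expansion. The only stated ratio, 80%/20%, is for the dialogues. Their expansion has a different trigger (ChatGPT failing to produce output), so it is not part of this point.

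**The concern.** One reading of the testing set does two jobs. It decides whether collection stops, and it shows whether the stage's primary goal is met. A module that falls short gets more data and, by implication, another test; a module that reaches the thresholds stops there. The figure in hand at stopping is thus always one that passed. Chance highs end the process and chance lows prolong it, so that figure is on average too high.

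Two things are at stake. The in silico accuracy could be reported as having met 90%/95% when the true accuracy is lower. Some modules could also go forward because of a favourable small sample.

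**Working it through.** **The plan's own figure.** The 50 cases per disease come without alpha, power, null value or precision, so there is nothing to reproduce. The 22 per disease in the same section belongs to the silent evaluation.

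**Inputs from the article.** Threshold: sensitivity ≥90% with specificity ≥95% (Hypotheses; Sample size calculation). Starting size: 50 image cases per disease. Stop when the threshold is met.

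**Assumptions, because the article does not give them.** Test positives: 10 (20% of 50) or 25 (50% of 50). True sensitivity: 80%, constant over rounds. Looks: up to three or five. Re-testing: either a fresh test set each round, or test cases pooled over rounds.

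**One look, 10 positives.** A pass needs at least 9 correct:

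P(X ≥ 9) = P(9) + P(10) = 0.268 + 0.107 = 0.376.

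**Three looks, fresh sets.** 1 − (1 − 0.376)³ = 0.757.

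**Three looks, pooled (10, 20, 30 cases; 9, 18, 27 correct needed).**
- Fail at 10, pass at 20: this needs exactly 8 of 10, then 10 of 10. 0.302 × 0.107 = 0.032.
- Fail at 10 and 20, pass at 30: this needs 17 of 20 without an earlier pass, then 10 of 10. (0.302 × 0.268 + 0.201 × 0.107) × 0.107 = 0.103 × 0.107 = 0.011.
- Total: 0.376 + 0.032 + 0.011 = 0.419.

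**25 positives.** A pass needs at least 23 correct: P(X ≥ 23) = 0.098. Three fresh looks: 1 − (1 − 0.098)³ = 0.267.

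| Test positives | One look | Three looks, pooled | Three looks, fresh | Five looks, pooled | Five looks, fresh |
|---|---|---|---|---|---|
| 10 | 0.38 | 0.42 | 0.76 | 0.43 | 0.91 |
| 25 | 0.10 | 0.12 | 0.27 | 0.12 | 0.40 |

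**Mean sensitivity on passing, 10 positives.** At one look: (0.9 × 0.268 + 1.0 × 0.107) / 0.376 = 0.929, against a true 0.80. Fresh looks leave this at 0.929, and three pooled looks give 0.926. The gap of about 13 points is therefore already present at one look. Repeated looks change how often a module passes, not how inflated a pass is.

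**Adding specificity ≥95%.** Assume 40 negatives and true specificity 0.95. At most 2 false positives are allowed, which has probability 0.677. One look: 0.376 × 0.677 = 0.254. Five fresh looks: 1 − (1 − 0.254)⁵ = 0.769. Five pooled looks, by simulation: 0.31.

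**A module that improves.** Let true sensitivity rise over five rounds (0.75, 0.80, 0.85, 0.88, 0.90). By simulation with fresh sets, the mean reported value on passing is 0.93 against a mean true value of 0.82 at stopping (10 positives), or 0.94 against 0.86 (25 positives). The bias shrinks but remains.

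**Comparison.** With 50 locked positives read once, a module with true sensitivity 0.80 shows ≥90% with probability 0.048.

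**The case against.** The strongest reply is that iterating until a target is met is ordinary model building. The stage's stated aim is to develop the system, and Hypotheses speaks of a goal here but of a primary outcome for the two later stages. That has some force, but the same paragraph gives the stage a secondary outcome, so its figures are set up as results. Iterating is not the fault. Reading the result at the iteration that passed is.

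The reply is also right on several points of size:
- Enlarging one data set most naturally means pooling, and then repeated looks add little (0.38 to 0.42).
- Ten test positives is the smallest case considered, and a constant 80% ignores the purpose of adding training data.
- The joint specificity condition lowers the pass probabilities.
- Re-testing is implied, not spelled out. A condensed article may leave the partition details to a fuller document. The stop-on-success rule itself, however, is stated.

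Two stronger readings are tempting and are not supported. A reader might infer that almost any module will eventually be reported as passing. That needs a small fresh test set each round with earlier results set aside, which the article does not say; with pooled cases the chance levels off near 0.43 in the 80%, 10-case example. A reader might also infer that the study's clinical accuracy estimates are inflated. They are not selected by this rule: the silent evaluation takes 100 new cases, and the early clinical evaluation takes new patients within predefined date ranges at three sites. Nor does the rule put standard care at risk, since the article says that standard management is not disrupted.

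**Conclusion.** The point stands in limited form. The stated rule ends expansion on the criterion that is also the in silico primary goal, with no test set named outside the process. Sensitivity and specificity read at the passing look are therefore biased upward.

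The direction does not depend on the assumptions: the upward bias appeared in every variant examined. The size does depend on them. For a true sensitivity of 80%, the chance of showing ≥90% within three looks runs from 0.12 (25 positives, pooled) to 0.76 (10 positives, fresh), before the specificity condition lowers it. The mean on passing is about 93%, nearly all of it from conditioning on a pass in a small test set.

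The damage is confined to the in silico figures and to which modules go forward. It should be corrected, but it does not threaten the two evaluation stages.

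**What to change.** In Sample size calculation, state that the testing set which steers expansion is a tuning set. For each disease, set aside in advance a fixed number of separate cases from the same 2020–2023 records, unused in any earlier look. Score each locked module on them once, and report sensitivity and specificity with 95% intervals whether or not they reach 90%/95%.

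If a disease has too few further images, report its in silico figures as development results only, and do not claim that the 90%/95% goal was met.

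The cost is some extra retrospective images and a few sentences of protocol text; prospective recruitment does not change. The in silico figures may be lower. A module exactly at the goal can also miss it by chance: with 50 locked positives and a true sensitivity of 0.90, the observed value reaches 90% with probability 0.616. This is a further reason to report the interval and not only pass or fail.
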